### Data analyses

#### Statistical analyses

The analysis of this study will be calculated as a mixed-effects model with the BSS total symptom score as the outcome variable. Mixed models are especially suited for longitudinal studies as they can deal with a correlated data structure and can analyze all cases and data points, even if missing values occur in the course of the trial. In detail, participants will be modeled as a random factor, while time and intervention (CAMS vs. TAU) as well their interaction will be modeled as fixed factors. The hypothesis that CAMS is superior to TAU in the treatment of suicidal patients will be evaluated by the significance test of the interaction effect time × intervention.

In case of a significant interaction effect, two planned general linear hypotheses will be calculated as post-hoc tests for linear mixed effect models in order to test between-group differences at t_2_ and t_3_. *P*-values will be adjusted for multiple comparisons following the Holm procedure.

We will perform an intention-to-treat analyses, that is, all trial participants will be analyzed as randomized, even if they discontinue treatment or are unavailable for one or both of the follow-up interviews. The between-group effect size (Cohen’s d) will be calculated at each follow-up assessment (t_2_ and t_3_).

Continuous secondary outcome measures (BDI-II, SCL-18-Mini, B-RFL, D-STAR-P) are analyzed in the same way. In absence of a valid cut-off score for clinically significant change or treatment response of the BSS, the number of subjects with clinically significant improvement as well as worsening based on the reliable change index (RCI) will be compared between groups using χ2 –tests or Fisher’s exact tests. For this purpose, the RCI will be calculated based on the pre-treatment scores of the study sample. We will use two-tailed tests for statistical significance with alpha set at *P* < 0.05. Effect strength will be determined with Cohen’s d. All calculations will be performed using SPSS 20.0 computer software [48].

We also investigate whether there is a correlation between the number of sessions and the effect of the therapeutic treatment using a correlation analysis.

Interim analyses before the completion of the investigations are not intended. Any potential deviations from the original statistical plan as defined in the study protocol will be described in protocol amendments as well as in the final study report.

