## Outcomes of the trial

### Primary outcome

#### Suicidal ideation

#### Beck scale for suicide ideation (BSS)

The primary outcome in the trial is the change in suicidal ideation severity from baseline measure (t_1_) to post assignment (t_2)_ and the follow-up assignments (t_3_ and t_4_). Suicidal Ideation is measured at each assessment by the *German Version of the Beck Scale for Suicide Ideation* (BSS [23];). The Beck Scale for Suicidal Ideation is a self-report instrument for assessing the patient’s severity of suicidal tendencies. For this purpose, 21 statements on a rating scale ranging from 0 to 2 are evaluated as self-assessments and the frequency and seriousness of previous suicide attempts are reported. BSS questions are related to the participant’s wish to live, wish to die, frequency of suicidal ideations, perceived capability to carry out an attempt, extent of actual preparation, and similarly oriented queries. The responses of 19 BSS items are summed up to create an index of suicidal ideation ranging from 0 to 38 with higher scores reflecting greater ideation. The German scale has been found to be a valid and reliable measure of suicidal ideation [24]. The English version of the BSS is widely used in suicide research and has demonstrated predictive validity for suicide attempts and deaths by suicide [25]. The BSS is administered at all study time points.

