#### Treatment fidelity

The therapists in CAMS and TAU are a licensed psychotherapist and a psychologist (Msc.). The assignment to the therapist is consecutive, i.e. the clinician who conducted the admission interview will also be responsible for further treatment. Potential effects of the therapists will be analysed during the evaluation and using post-hoc analyses. We trained CAMS therapists with help of the E-learning training by [name], which both therapists have completed before the start of the study. Additionally, both have worked intensively with the CAMS manual written by [name]. The administration of the Suicide Status Form (SSF) was practiced by each therapist with at least 3 patients in a pilot phase prior to the start of the study. This methodology ensured that the therapists internalized both the content and process of CAMS demonstrating sufficient adherence to the CAMS framework. In the event of difficulties, [name] provides consultation.

Every fourth treatment session of the therapists is supervised. Each therapy session is audiotaped, and the therapists are rated for adherence according to the CAMS Rating Scale (CRS) by an external evaluator so optimal treatment adherence to CAMS is ensured [46]. The supervisors also monitored the E-TAU sessions using the CRS to ensure and verify that clinicians were not doing CAMS procedures in these sessions thus ensuring experimental fidelity. The CRS is an observer rating scale and consists of three parts and 14 items in total. Part I covers the treatment philosophy, part 2 the clinical/ session framework and part 3 the overall rating. The items were rated on a 6-point scale from 0 = poor to 6 = excellent. The use of the CRS therefore serves to confirm the difference in treatment groups with regard to the fact that the same therapists are treating both groups. We discussed the problem of the CAMS therapists being also the TAU therapists and the question if how the therapy is influenced by the knowledge about the other therapy arm. But in fact, despite the risk of contamination were mitigated by review of videos and use of the CRS. Any experimental between-group differences would provide clear proof of an experimental effect as the clinicians serve as their own control (removing a tremendous source of error variance seen in other RCT’s that use different clinicians in each arm of the trial).

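### Baseline BSS is used only as a repeated outcome, so the primary interaction test and the t2/t3 contrasts forgo baseline adjustment and respond in opposite directions to a chance baseline gap

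*Protocol article*

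**What the plan says.** The Statistical analyses section sets out the primary model term by term: "participants will be modeled as a random factor, while time and intervention (CAMS vs. TAU) as well their interaction", the last three as fixed factors. Superiority of CAMS "will be evaluated by the significance test of the interaction effect time × intervention". If that test is significant, two further hypotheses are tested "in order to test between-group differences at t_2_ and t_3", with Holm adjustment. The continuous secondary outcomes are analysed in the same way.

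On the outcome itself, the BSS section states: "The primary outcome in the trial is the change in suicidal ideation severity from baseline measure", to be followed through t2, t3 and t4. It adds: "The BSS is administered at all study time points". Under Trial design and Randomization, the t1 questionnaires are completed before the die is thrown. No stratification or blocking is described.

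The model has no baseline covariate and no constraint that the arms share a t1 mean.

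**The concern.** Since the outcome is change from t1 and time is a factor, the natural reading is that t1 is one of four levels of time, with a separate mean in each arm. Two consequences follow.

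- The interaction that serves as the primary test, and as the gate, compares change from t1 between arms. Simple change subtracts the whole baseline gap, although only the fraction rho of it is expected to persist. It therefore over-corrects.
- The t2 and t3 contrasts, as worded, are plain differences between arms at those visits. They take no account of the baseline gap.

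The two steps of one decision rule thus estimate different quantities, and both are less precise than a baseline-adjusted comparison using data the trial already collects. The protocol's Discussion calls the sample quite small and says a large effect is needed to detect a difference, so precision matters here.

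**Working it through.** **Inputs from the protocol.** Planned d = 1 and 30 per arm (Power analysis and sample size calculation); two-sided 5% (Statistical analyses); allocation by die (Randomization).

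**Assumed, not in the protocol.** Baseline-follow-up correlation rho of 0.3, 0.5 or 0.7; equal SD at each visit (set to 1); complete data.

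**The plan's own figure.** The plan gives no figure for the precision of these contrasts. Its total of 48 does not follow from d = 1, one-sided 5% and 80% power, which gives 14 per group (28 in all) for a two-sample t-test. That is a separate matter; only d = 1 and 30 per arm are used here.

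**Step 1: variances.** In units of 2/n per contrast:

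- plain difference at a visit: 1
- difference in change from t1: 2(1 − rho)
- baseline-adjusted difference: 1 − rho²

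Adjusted over change is (1 − rho²) / [2(1 − rho)] = (1 + rho)/2. Adjusted over plain is 1 − rho².

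| rho | plain | change | adjusted | adjusted/change | adjusted/plain |
|---|---|---|---|---|---|
| 0.3 | 1.00 | 1.40 | 0.91 | 0.65 | 0.91 |
| 0.5 | 1.00 | 1.00 | 0.75 | 0.75 | 0.75 |
| 0.7 | 1.00 | 0.60 | 0.51 | 0.85 | 0.51 |

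**Step 2: size of a chance gap.** The SE of the baseline difference is √(2/30) = 0.258 SD. P(|gap| > 0.3) = 2[1 − Φ(0.3/0.258)] = 0.245. The 95% range is ±1.96 × 0.258 = ±0.51 SD.

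**Step 3: effect of a gap g.** The plain contrast shifts by rho × g and the change contrast by −(1 − rho) × g. For g = 0.3 SD:

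| rho | plain | change |
|---|---|---|
| 0.3 | +0.09 | −0.21 |
| 0.5 | +0.15 | −0.15 |
| 0.7 | +0.21 | −0.09 |

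Given g = 0.5, near the edge of the 95% range, take the plain contrast at rho 0.5 under the null. Its mean is 0.25, its conditional SD is √(0.75 × 2/30) = 0.224 and the critical value is 1.96 × 0.258 = 0.506. The conditional rejection rate is 1 − Φ[(0.506 − 0.25)/0.224] = 13%. At rho 0.3, 0.5 and 0.7 the rates are 8%, 13% and 20% for a single plain contrast, and 16%, 13% and 10% for a single change contrast. Averaged over all possible gaps, each returns to 5%.

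**Step 4: power for one post-baseline visit, 30 per arm.** Power = Φ(d/√(2v/n) − 1.96), with v the relevant variance from step 1. Example: d = 0.7, rho 0.3, change: 0.7/√(2 × 1.40/30) = 2.29, and Φ(0.33) = 63%.

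| rho | d = 1, change → adjusted | d = 0.7, change → adjusted |
|---|---|---|
| 0.3 | 91% → 98% | 63% → 81% |
| 0.5 | 97% → 99% | 77% → 88% |
| 0.7 | over 99% for both | 94% → 97% |

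The plain contrast has 97% (d = 1) and 77% (d = 0.7) at every rho. The actual gate is a joint test over the visits, so these single-visit figures illustrate the loss rather than give the exact power of the planned test.

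**The case against.** **Baseline is not ignored.** A reader might infer that t1 plays no part in the primary test. It does: the interaction compares change from t1. The fair criticism is that it uses t1 inefficiently.

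**Chance imbalance is not bias.** A reader might infer that the tests are biased or exceed 5%. Under randomisation each contrast is unbiased and holds 5% on average. The t2/t3 tests also run only after a significant interaction, with Holm adjustment, and a gap pushes the two steps in opposite directions. In a null simulation (30 per arm, equal correlations, complete data, rho 0.3 to 0.7), the chance of passing the gate and then finding at least one significant contrast was about 1%, both overall and given a gap above 0.3 SD. This disposes of any claim about the error rate of the two-step procedure. It does not stop a given trial's estimates from being displaced.

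**Power is adequate as planned.** At d = 1 with 30 per arm the planned analysis already has about 91% or more for rho of 0.3 and above. That stands. However, d = 1 was obtained by subtracting two within-arm effects, and the protocol says the interaction effect was not reported. The Discussion also expects that including chronic patients may reduce effects.

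**Covariance.** A reader might infer that a participant random factor forces equal variances and correlations and so inflates error at t4. The article states no residual covariance, a detail commonly left to an analysis plan, and no t4 contrast is planned.

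**Therapist.** A reader might also fault the absence of a therapist term. The Treatment fidelity section says "Potential effects of the therapists will be analysed during the evaluation and using post-hoc analyses", so it is not left to post-hoc work alone. With two therapists treating both arms, and an assumed 2% to 10% of variance between them, the term would cut the standard error by only about 1% to 5%. What that section concludes from shared clinicians is a question of interpretation, separate from this one.

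**Conclusion.** The point holds as one of efficiency and consistency, minor to moderate in weight. The stated model leaves out adjustment for a baseline measured in every randomised patient before allocation, and its gate and follow-up contrasts estimate different quantities. The adjusted variance is 65% to 85% of the change contrast and 51% to 91% of the plain contrast. A quarter of such trials would have a baseline gap above 0.3 SD, enough to move the two kinds of estimate by 0.09 to 0.21 SD in opposite directions. The effect on power is small at the planned d = 1 and material if the true effect is nearer 0.7.

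These sizes rest on rho between 0.3 and 0.7, equal SDs across visits and complete data, none of which the protocol gives. The direction does not depend on the value chosen: within this range adjustment is more precise than either alternative. The conclusion also rests on reading t1 as a level of time and the t2/t3 tests as plain differences, which is the natural reading of the text but is not spelled out.

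**What to change.** Use one baseline-adjusted model, in either form:

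- keep t1 to t4 as outcomes, but constrain the t1 mean to be equal across arms; or
- model BSS at t2, t3 and t4 with intervention, time and their interaction, plus t1 BSS and t1 BSS × time as covariates.

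Take the primary test and the t2 and t3 contrasts from that same model. In the second form, state the primary test as the joint test of the arm differences at t2 to t4. The interaction alone would there ask only whether the effect varies between visits, and would miss an effect that is the same at each. Treat the continuous secondary outcomes alike where a t1 value exists.

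The cost is a change of wording and a few degrees of freedom. No new data are needed. The change should be recorded as an amendment, as the protocol itself requires for departures from its statistical plan.

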### Trial design

In our pragmatic randomized controlled trial at the Clinic of Psychiatry and Psychotherapy, Ev. Hospital Bethel, Germany, CAMS is being compared to E-TAU within an inpatient crisis setting. The trial is designed as a single-center, two-armed, parallel-group, observer-blinded randomized clinical effectiveness trial. Since we assume that about 50% of the patients we initially examine do not meet the inclusion criteria, 20% do not consent to participate in the study and 20% discontinue treatment, we plan to examine 144 patients of the Clinic who are admitted to the ward due to acute suicidal risk (thoughts or behaviors) in order to obtain our target sample size of 60 patients. After screening and randomizing, the study participants will be followed for about 6 months at four checkpoints t_1_, t_2_, t_3,_ t_4_.

Individuals who are screened positive for the trial and who gave their written informed consent to take part in the study are asked to complete a set of questionnaires (t_1_) on the admission day or on the workday following the admission day. Then, the patient is randomized and informed about their group membership and the respective interventions begin on the following day. A second follow up assessment (t_2_) is carried out between 10 and 40 days later at the day before discharge. Another follow-up assessment will be arranged for 4 weeks after discharge (t_3_). Five months after the end of treatment, patients will receive the assessment instruments again by mail (t_4_). Refer to Fig. 1 for a schematic overview of the time flow of the trial and see Appendix 1 for the complete review of the study questionnaires.

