#### Therapeutic relationship

#### German version of the scale to assess the therapeutic relationship in community mental health care, patient-version (D-STAR-P)

The quality of the therapeutic relationship will be assessed by the patient-version of the D-STAR. The D-STAR-P is a 12-items self-report questionnaire with three subscales: Positive Collaboration, Positive Clinician Input, and Nonsuppurative Clinician Input. Loos et al. (2011) found the psychometric properties to be acceptable [36]. The feasibility and internal consistency of the D-STAR-P was good and there is evidence of good convergent validity.

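### The therapeutic relationship (D-STAR-P) is judged by a gated time × intervention interaction, although t1 comes before any study therapy; ungated group comparisons at t2 and t3 would suit it better

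*Protocol article*

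**What the plan says.** All references are to the protocol article.

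- **Deciding test (Statistical analyses).** For the primary outcome, the BSS, superiority "will be evaluated by the significance test of the interaction effect time × intervention".
- **Gate (same section).** "In case of a significant interaction effect, two planned general linear hypotheses will be calculated as post-hoc tests", and these compare the groups at t2 and t3 with Holm adjustment. Cohen's d between groups is not gated; it "will be calculated at each follow-up assessment", that is, at t2 and t3.
- **Extension to the D-STAR-P (same section).** "Continuous secondary outcome measures (BDI-II, SCL-18-Mini, B-RFL, D-STAR-P) are analyzed in the same way".
- **Timing of t1 (Trial design).** Screened and consenting patients "are asked to complete a set of questionnaires (t_1_) on the admission day or on the workday following the admission day". After that, "the patient is randomized and informed about their group membership and the respective interventions begin on the following day".
- **Contact before therapy (Treatment fidelity).** Therapists are assigned consecutively: "the clinician who conducted the admission interview will also be responsible for further treatment".
- **The instrument (Therapeutic relationship).** "The quality of the therapeutic relationship will be assessed by the patient-version of the D-STAR". That section names no time points.

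The effect of CAMS on the therapeutic relationship is a named secondary aim (Aim of the trial).

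**The concern.** The BSS, BDI-II, SCL-18-Mini and B-RFL describe states or attitudes that a patient brings to admission. A pre-randomisation value is then a natural baseline, and a treatment effect shows as a difference in change over time.

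The D-STAR-P is different in kind. It rates a relationship with a clinician, and at t1 the patient has had no study therapy in either arm. A t1 rating, if there is one, can reflect little more than the admission interview. If there is none, the interaction asks only whether the group difference changes after t2, not whether the arms differ.

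A non-significant interaction also closes the planned t2 and t3 tests. A null result could then be reported as no effect on the therapeutic relationship when the rule itself was poorly placed to find one.

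**Working it through.** **Inputs.** From the article: two-sided 5% tests (Statistical analyses); 24 per group as the calculated size and 30 as the target (Power analysis and sample size calculation). Assumed, because the article gives no such figures for the D-STAR-P: d = 0.8 unless stated otherwise, a lasting difference after t1, equal correlation ρ between all visits (compound symmetry), equal variances and no missing data. The article states no power for the D-STAR-P, so there is no figure of its own to reproduce; its sample size calculation concerns the BSS.

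**Step 1: D-STAR-P first given at t2.** Let the group difference be δ at every visit. Each time contrast of that difference is δ − δ = 0, so the noncentrality of the interaction test is 0 and its rejection rate equals alpha, whatever δ, n or ρ. Simulation of the t2–t3 model agrees: at 30 per arm, with d from 0.5 to 1.0 and ρ from 0.3 to 0.7, the interaction rejected in 4.6% to 5.7% of runs.

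On the same kind of data a group comparison is sensitive:
- t2 difference, noncentral t with noncentrality d√(n/2) and 2n − 2 degrees of freedom. For n = 24: 0.8 × √12 = 2.77, power 77%. For n = 30: 0.8 × √15 = 3.10, power 86%.
- Group effect averaged over t2 and t3, simulated at 30 per arm: 53–66%, 91–97% and 98–100% for d = 0.5, 0.8 and 1.0.

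Because of the gate, the planned t2 and t3 tests would open in only about 5% of such trials.

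**Step 2: D-STAR-P also given at t1.** Randomisation makes the expected t1 difference zero, so over t1–t3 the differences are (0, d, d). Their squared deviations from the mean 2d/3 sum to (4/9 + 1/9 + 1/9)d² = (2/3)d². The interaction F test then has noncentrality λ = (n/2)(2/3)d²/(1 − ρ) = nd²/[3(1 − ρ)], with 2 and 2(2n − 2) degrees of freedom. For n = 30, λ = 6.4/(1 − ρ).

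The t2 comparison with t1 as covariate has noncentrality d√(n/2)/√(1 − ρ²) and 2n − 3 degrees of freedom.

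| ρ | λ (n = 30) | Interaction, n = 30 | t2 adjusted for t1, n = 30 | Interaction, n = 24 | t2 adjusted for t1, n = 24 |
|---|---|---|---|---|---|
| 0.1 | 7.11 | 65% | 87% | 55% | 78% |
| 0.3 | 9.14 | 77% | 89% | 66% | 81% |
| 0.5 | 12.80 | 90% | 94% | 81% | 88% |
| 0.7 | 21.33 | 99% | 99% | 96% | 97% |

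For a smaller effect (d = 0.5, 30 per arm, ρ = 0.3), simulation gave 37% for the interaction and 66% for the group effect averaged over t2 and t3.

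**Step 3: allowing for Holm.** The table tests t2 alone at 5%. With two Holm-adjusted tests, the least favourable level for t2 is 2.5%. The same formula at 30 per arm then gives 79%, 82% and 90% at ρ = 0.1, 0.3 and 0.5, against 65%, 77% and 90% for the interaction. At ρ = 0.7 it gives 98% against 99%. These are lower bounds, since t2 is tested at 5% whenever t3 is the first to be rejected.

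**The case against.** The strongest reply is that the worst case depends on a schedule the reader cannot see. Fig. 2 and Appendix 1 are not shown, which is no fault of the plan. The visible text leans, if anything, towards a t1 rating: the Abstract counts admission among the four assessments and lists the therapeutic relationship among the measures given at assessment timepoints, and the Exploratory measures section gives the same completion time for all four batteries. Against that, only the BSS is explicitly said to be given at every time point. The question stays open, so the 5% figure must stay conditional, both on there being no t1 rating and on the advantage staying constant after t2.

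A second reply is that with a t1 rating the planned test does well once the correlation is 0.5 or more. It then beats the unadjusted t2 difference (90% against 86% at 30 per arm, ρ = 0.5). That is correct, but the advantage disappears when t1 is used as a covariate (94%).

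A third is that an advantage would not vanish from the report, because Cohen's d at t2 and t3 is ungated. This also stands; what is lost is a planned test.

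A reader might infer that no relationship at all exists at t1, or that a real CAMS advantage would generally be missed. The article supports neither. The admission interviewer becomes the therapist, and a t1 rating would let the interaction detect a later difference. Nor does the article make the relationship the mechanism under test here: it describes CAMS as intended to strengthen the alliance and leaves mechanisms to later studies.

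**Conclusion.** The point holds in a limited form. The article fixes an analysis for the D-STAR-P that suits it poorly, because the deciding test leans on a time point before any study therapy and gates the comparisons that matter.

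The size depends on the schedule. Without a t1 rating, a constant advantage is rejected only at alpha; this is algebra and needs no assumed effect size or correlation. With one, the loss at d = 0.8 and 30 per arm is about 22, 12 and 4 percentage points at correlations 0.1, 0.3 and 0.5, and is negligible at 0.7. Holm adjustment narrows these gaps and at the lower bound closes them by 0.5.

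The effect size, correlations, compound symmetry and complete data are assumptions. The primary outcome and the other secondary outcomes are not affected by this point.

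**What to change.** Take the D-STAR-P out of the sentence that extends the BSS analysis to the secondary outcomes, and give it its own. Within the mixed model, estimate and test the between-group differences at t2 and t3, Holm-adjusted and not conditional on the interaction. If a t1 rating exists, enter it as a covariate only, not as an outcome visit. State in the text at which visits the D-STAR-P is given.

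The change needs no new data or visits. It keeps the mixed model, both planned comparison times and the Holm procedure. The costs are that one secondary outcome is analysed differently from the others and that, at a high correlation with t1, Holm adjustment may give back about one percentage point of power. Recruitment has already begun, so record the change as an amendment, as the article itself provides for deviations, and before outcome data are examined by arm.
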